### Perioperative management, discharge, and follow-up

Perioperative thrombosis prophylaxis will be performed according to current German guidelines
[13]. Single-shot antibiotics (ampicillin/sulbactam) will be given 30 minutes before surgery. Intraoperative anesthesia will comprise intravenous administration of piritramide. Postoperatively, pain medication will be administered according to the World Health Organization (WHO) analgesic ladder based on the judgment of the treating ward physician beginning directly after surgery in the recovery room
[14]. Nonsteroidal anti-inflammatory drugs (metamizol) will be administered solely or in combination with a weak (tilidine) or strong opioid (piritramide, oxycodone). Peridural analgesia is not part of the pain management in this study. On the day of surgery and POD 1, analgesics will be administered intravenously. Beginning from POD 2, analgesics will be applied orally in cases of tolerated oral intake. Daily blood samples are scheduled for POD 1 to 5. Patients will be encouraged for discharge from POD 5 onward upon complete fulfillment of the discharge criteria (see ‘Discharge criteria’). Patients who receive the experimental intervention will be recommended to attend an ambulatory gynecological checkup 10 days after surgery. All patients will be followed up at an ambulatory checkup scheduled 3, 12, and 36 months after surgery. The ambulatory checkup will comprise taking a history, a clinical examination, and an assessment of secondary endpoints. Patients will be notified in writing and by phone in case they fail to return for their follow-up visits. If reaching the patients directly is not possible, their general practitioner will be contacted. Missing follow-up data will then be completed by phone.

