#### Secondary endpoints

Secondary endpoints will be measured intraoperatively, at daily study visits, and 3, 12, and 36 months postoperatively. Intraoperative parameters comprise operation time, length of minilaparotomy, height of the anastomosis and the length of the unfixed specimen. The number of harvested lymph nodes will be determined postoperatively by pathological examination. The schedule for study visits and follow-up is provided in Table 
2. Pain intensity will be measured at rest and during mobilization in the same way as the primary endpoint. The dose and identity of applied analgesics will be recorded daily. Daily analgesic use will be graded using a numeric scale from one to three according to the WHO analgesic ladder
[14]. Cumulative analgesic use will be assessed by adding daily WHO analgesic ladder scores. Daily patient mobility will be measured in meters by an electronic pedometer device, which will be placed on the wrist of the nondominant hand of the patient. Cumulative patient mobility will be assessed by adding daily distances. Inflammatory parameters (leukocytes, C-reactive protein) will be measured daily from POD 1 to POD 5. The discharge criteria (See ‘Discharge criteria’) will be evaluated beginning from POD 5. After discharge, the patients will be asked to record daily analgesic use and activity on a scale ranging from 0 (inactivity) to 5 (return to usual activities) until they return to usual activities and stop pain medication on a standardized form, which will be evaluated at the 3-month follow-up visit. Morbidity according to Dindo *et al*.
[20] will be assessed at discharge, 3, 12, and 36 months postoperatively. The following patient-reported outcomes will be assessed preoperatively and 3, 12, and 36 months postoperatively: quality of life measured by the Gastrointestinal Quality of Life Index (GIQLI)
[21], sexual function measured by the Female Sexual Function Index (FSFI)
[22], and cosmetic satisfaction measured by the Body Image Scale
[23].

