**Table 2 Tab2:** **Postoperative outcome parameters and schedule of study visits and follow-up**

Outcome parameter	Daily in-hospital study visits				Follow-up		
	POD 1 (24h) ^*^	POD 2 to POD 5	≥ POD6	Discharge	3 months	12 months	36 months
Pain intensity (VAS)	X (primary outcome)	X	X	X			
Daily analgesic use	X	X					
Cumulative analgesic use		X (POD 5)^†^		X	X		
Daily patient mobility	X	X		X			
Cumulative patient mobility				X			
Inflammatory parameters (CRP, leukocytes)	X	X					
Discharge criteria		X (POD5)^†^	X				
Length of stay				X			
Morbidity				X	X	X	X
Return to normal activities					X		
Quality of life (GIQLI [21])					X	X	X
Sexual function (FSFI [22])					X	X	X
Cosmetic satisfaction (Body Image Scale [23])					X	X	X

^*^Study visit on POD 1 is scheduled 24 hours postoperatively; ^†^parameters will be measured solely on POD 5. CRP, C-reactive protein; FSFI, Female Sexual Function Index; GIQLI, Gastrointestinal Quality Of Life Index; POD, postoperative day; VAS, visual analogue scale.

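### Cumulative mobility is summed to discharge, so a shorter stay lowers the total and can mask, or in some circumstances reverse, a true daily mobility gain

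*Protocol article*

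**What the plan says.** Under Secondary endpoints, the protocol article states that "Daily patient mobility will be measured in meters by an electronic pedometer device" and that "Cumulative patient mobility will be assessed by adding daily distances". It names no window and no averaging per day.

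In Table 2 the row "Cumulative patient mobility" has a single entry, in the Discharge column. The daily mobility row has entries at POD 1, POD 2 to 5 and Discharge, and none at POD 6 or later.

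Under Perioperative management, "Patients will be encouraged for discharge from POD 5 onward upon complete fulfillment of the discharge criteria". The Discharge criteria include adequate pain control during mobilization, full oral intake, wound healing and falling inflammatory markers.

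Cumulative analgesic use is handled differently. Table 2 gives it a POD 5 time point, whose footnote reads "parameters will be measured solely on POD 5", as well as discharge and 3-month time points.

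**The concern.** A sum over a stay of variable length combines two things: how far the patient walks per day, and how many days she is counted. The second depends on recovery, because discharge requires recovery criteria to be met. Length of stay is already a secondary endpoint in its own right.

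The two parts pull against each other. The protocol expects faster convalescence with NOTES, and its Discussion lists pedometer mobility among the outcomes that reflect recovery, so a higher total reads as better. A patient who recovers sooner goes home sooner and loses days from her total, and no pedometer distance is scheduled after discharge. A real benefit on one recovery outcome therefore lowers the score on another.

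**Working it through.** **Inputs from the protocol article.** Total = sum of daily distances, evaluated at discharge; earliest discharge POD 5; 29 patients per arm. The article gives no figure for mobility. Its sample size is for the primary endpoint and reproduces (t test, effect size 1, power 0.90: 22.02, rounded up to 23; 23 / 0.8 = 28.75, rounded up to 29), but this point does not depend on it.

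**Assumed inputs.** Daily distances, their variation and the distribution of stay are not in the documents.

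**Step 1: when the total reverses.** Let NOTES patients walk a fraction g more every day, with stays L_N and L_C.
- Constant daily distance: ratio of totals = (1 + g) × L_N / L_C.
- Distance rising in proportion to POD: ratio = (1 + g) × L_N(L_N + 1) / [L_C(L_C + 1)].
- Rising distance, summing only the days Table 2 schedules (POD 1 to 5 plus the discharge day): the control total is the POD 1 to 5 sum plus one further day.

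Take g = 0.20, L_N = 5 and, where distance rises, 100 m × POD. The NOTES total is then 1.2 × 1500 = 1800 m.

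| Control discharge | Rising, all days | Constant, all days | Rising, as scheduled |
|---|---|---|---|
| POD 6 | 1800/2100 = 0.86 | 6/6 = 1.00 | 1800/2100 = 0.86 |
| POD 7 | 1800/2800 = 0.64 | 6/7 = 0.86 | 1800/2200 = 0.82 |
| POD 8 | 1800/3600 = 0.50 | 6/8 = 0.75 | 1800/2300 = 0.78 |

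The true daily ratio is 1.20 throughout, and a POD 1 to 5 sum returns 1.20 whatever the stay.

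**Step 2: the reading of Table 2 matters.** A patient at 1000 m/day discharged on POD 5 totals 5 × 1000 = 5000 m. One at 750 m/day discharged on POD 8 totals 8 × 750 = 6000 m if every day counts, but 6 × 750 = 4500 m if only the scheduled days count. The order of the two patients depends on a rule the article does not state.

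**Step 3: simulated trials.** 29 per arm, NOTES 20% more metres per day, log-normal variation between patients (SD 0.4 on the log scale), two-sided Mann-Whitney U test at 0.05. Stay is 5 + Poisson, with means 1 v 2 for the one-day difference and 1.5 v 2 for the half-day difference. Ranges are across repeated runs.

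| Scenario | Slower arm has larger median | Slower arm significantly favoured | NOTES significantly favoured | Same, POD 1 to 5 sum |
|---|---|---|---|---|
| One day shorter, rising, all days | 71–74% | 9–10% | 0.4–0.6% | 36–38% |
| One day shorter, rising, as scheduled | 30–32% | 0.5% | 8–8.5% | 36–38% |
| One day shorter, constant distance | 41% | 1.2% | 4% | 35% |
| Half a day shorter, rising, all days | 39–40% | 0.9% | 4–5% | about 38% |
| Equal stay, rising, all days | – | 0.1% or less | 22–26% | 36–39% |

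With equal stay the loss of power comes only from the added variation in days counted.

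**Step 4: other inputs** (log-SD 0.5, rising distance, all days, mean stay 5.5 v 6.5 days). With no true daily difference, the to-discharge sum significantly favours the slower arm in 46% of runs, while the fixed window keeps about 5% two-sided error. With a 40% daily gain the wrong direction is rare (1.2%), but significance in favour of NOTES falls from 69% to 5%.

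**The case against.** The other side has several fair points.

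- **Reversal is not the general result.** A reader might infer that the endpoint will usually point the wrong way, as in the 71 to 74% scenario. The documents do not support that. It needs a full day's difference in mean stay, distance that rises with time and every inpatient day counted. Under the other readings with a shorter NOTES stay, the slower arm has the larger median in 30 to 41%, and a significant wrong result occurs in about 0.5 to 1.2%. What stands is the loss of a true effect, which appears in every scenario with a shorter NOTES stay.
- **The total can be formed.** A reader might take the gap at POD 6 and later in Table 2 to mean that no discharge total is possible. The text says mobility is measured daily without an upper limit, and Table 2 does include the discharge day. The gap makes the rule unclear; it does not make the sum impossible.
- **Analgesics are different.** It is tempting to extend the point to "Cumulative analgesic use". The protocol says "Cumulative analgesic use will be assessed by adding daily WHO analgesic ladder scores", so a longer stay also raises that total. But a higher analgesic total reads as worse, so the slower arm looks worse, which is the expected direction and partly genuine use. Dose and identity are recorded daily, the diary continues after discharge, and a fixed POD 5 total already exists.
- **The test is an assumption.** Mobility is not named in the list of continuous secondary endpoints analysed by Mann-Whitney, and an analysis plan may treat it otherwise. The definition itself, however, is stated in both text and table.
- **The reach is small.** Daily mobility on POD 1 to 5 and length of stay are separate outcomes and would show a true gain.

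**Conclusion.** The point holds for cumulative mobility. The stated definition makes the total rise with length of stay, and stay depends on recovery. If NOTES shortens stay, a true daily gain is diluted or masked, and it reverses when the stay difference outweighs the gain.

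For a 20% daily gain and a half-day to one-day shorter mean stay, significance in favour of NOTES is about 0.5 to 8%, against about 35 to 38% with a fixed window. The slower arm has the larger median in about 30 to 74% and is significantly favoured in about 0.5 to 10%. With equal stay a significant reversal is very rare, but power still falls, to about 24% against 39%. All these figures rest on assumed distances and stays; the direction of the distortion does not.

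This concerns one derived secondary endpoint. The primary endpoint, the sample size and the daily POD 1 to 5 mobility data are unaffected. It should be corrected, but it does not threaten the trial's main conclusion.

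**What to change.** Define cumulative patient mobility as the sum of daily distances over POD 1 to POD 5, and move its entry in Table 2 to POD 5. Those daily measurements are already scheduled, and patients discharged under the stated criteria are in hospital until at least POD 5. State how a part-day on POD 5 and early withdrawal are handled.

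Mean distance per observed day is an alternative, but it is best confined to POD 1 to 5. If distance rises with time, an average to discharge still grows with stay: in the Step 1 example, 1800/5 = 360 m/day for NOTES against 3600/8 = 450 m/day for a control patient discharged on POD 8.

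Report the to-discharge total only descriptively, next to length of stay, and say which days from POD 6 onward it includes, so that text and Table 2 agree.

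For analgesics, name the existing POD 5 total as the main between-arm comparison and keep the discharge and 3-month totals as they are.

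The cost is one definition and one or two table entries, with no new measurement.

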**Table 2 Tab2:** **Postoperative outcome parameters and schedule of study visits and follow-up**

Outcome parameter	Daily in-hospital study visits				Follow-up		
	POD 1 (24h) ^*^	POD 2 to POD 5	≥ POD6	Discharge	3 months	12 months	36 months
Pain intensity (VAS)	X (primary outcome)	X	X	X			
Daily analgesic use	X	X					
Cumulative analgesic use		X (POD 5)^†^		X	X		
Daily patient mobility	X	X		X			
Cumulative patient mobility				X			
Inflammatory parameters (CRP, leukocytes)	X	X					
Discharge criteria		X (POD5)^†^	X				
Length of stay				X			
Morbidity				X	X	X	X
Return to normal activities					X		
Quality of life (GIQLI [21])					X	X	X
Sexual function (FSFI [22])					X	X	X
Cosmetic satisfaction (Body Image Scale [23])					X	X	X

^*^Study visit on POD 1 is scheduled 24 hours postoperatively; ^†^parameters will be measured solely on POD 5. CRP, C-reactive protein; FSFI, Female Sexual Function Index; GIQLI, Gastrointestinal Quality Of Life Index; POD, postoperative day; VAS, visual analogue scale.

### Data management

Data will be entered in a CRF by the investigator or a designated representative of the respective center. Participant names and collected data are subject to medical confidentiality. In the case of resignation, collected data may be pseudonymized unless the participant explicitly requests that all data be erased. Data will be entered into the CRF as soon as possible after data retrieval. After completion, the original CRF will be sent to the SDGC for validation and transfer into the trial database. Double data entry will be performed in order to ensure accurate transfer from the CRF to the database. At the end of the trial, the original CRFs and final database will be archived by the principal investigator, who is responsible for providing data to trial investigators. All trial members are obliged to ensure the deletion of duplicate data recordings at the end of the trial.

### Safety and reporting of serious adverse events

Serious adverse events (SAEs), defined according to the guidelines for good clinical practice by the International Conference on Harmonization of Technical Requirements for Registration of Pharmaceuticals for Human Use (ICH-GCP), will be reported from the day of first enrollment until the regular end of the trial
[24]. All SAEs will be documented in a separate ‘serious adverse event form’ and the CRF, and will be reported to the principal investigator within 24 hours of being noted. If the principal investigator considers a SAE as unexpected and related to the study intervention, he will submit a report to the local ethics committee within 3 days. Furthermore, morbidity will be documented within the CRF. The study steering committee will meet to evaluate morbidity and SAEs at least twice: after randomization of one-third of the patients and after randomization of two-thirds of the patients. In the case of relevant imbalances between the groups, a report will be submitted to the local ethics committee. The trial may be terminated based on the decision of the principal investigator according to the assessment of the local ethics committee.

### Statistical methods

#### Sample size

Sample size was determined for the primary endpoint, the intensity of pain during mobilization measured on the VAS 24 hours after surgery. Park *et al*. reported a mean (± standard deviation) VAS score of 4.2 ± 1.7 for transvaginal hybrid NOTES vs. 5.7 ± 1.7 for conventional laparoscopic right-sided hemicolectomy
[10]. According to Gallagher *et al*. a standardized effect size of unity in the VAS score (difference in unity given a standard deviation of unity) is discriminable by patients and can be considered clinically relevant
[25]. We made the following assumptions when calculating the patient number:

 Hypothesis: transvaginal hybrid NOTES sigmoid resection causes less pain than laparoscopic-assisted sigmoid resection 24 hours after surgery (superiority analysis). Two-sided analysis with a type I error (α) of 0.05 and power (1-β) of 0.90. The standardized effect size was assumed to be 1 (difference in VAS of 1 and standard deviation of 1). The power was set at 0.90 because some evidence is already available.

Based on these assumptions, a sample size of 23 patients per arm was calculated using the R package (version 0.1-8;
http://cran.r-project.org/web/packages/Sample.Size/index.html, *t* test for two independent samples). Assuming a drop-out rate of 20%, the total number of patients needed per arm is 29, resulting in a total patient number of 58 patients for the primary arm.

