#### Statistical analysis

Statistical analysis will be performed using the R statistical software (
http://www.r-project.org). A two-sided *P* value <0.05 will be considered significant. For baseline characteristics, descriptive statistics will be used. For analysis of the primary outcome, a Mann-Whitney *U* test will be applied. For categorical secondary endpoints, chi-square statistics will be used. To compare continuous secondary endpoints (operating time, length of hospital stay, analgesic use, time to return to normal activity), Mann-Whitney *U* tests will be applied. No interim analysis is planned for this study. For the time course of pain at provocation and at rest, a mixed model with mean VAS scores will be applied.

Missing values will be replaced with the last available value (the last observation carried forward (LOCF) approach). Data from patients who withdraw from the study will be disregarded unless exclusion is based on postoperative patient wishes and the patient agrees to the use of the already obtained data.

The confirmatory analysis will be performed based on intention-to-treat (ITT) patients and with respect to ITT principles. A standard sensitivity analysis will be performed on the per-protocol population.

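### The 23 per arm is right for a standardized effect of 1, but equating that effect with 1 VAS point conflicts with the only observed SD quoted (1.7), so the 90% power is not anchored in VAS points

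*Protocol article*

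**What the plan says.** All the figures are in the protocol article under Statistical methods, Sample size.

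- An earlier comparison is reported first: "VAS score of 4.2 ± 1.7 for transvaginal hybrid NOTES vs. 5.7 ± 1.7 for conventional laparoscopic right-sided hemicolectomy".
- A second source is then cited for clinical relevance: "a standardized effect size of unity in the VAS score (difference in unity given a standard deviation of unity) is discriminable by patients".
- The error rates follow: "Two-sided analysis with a type I error (α) of 0.05 and power (1-β) of 0.90".
- The design effect is "The standardized effect size was assumed to be 1 (difference in VAS of 1 and standard deviation of 1".
- The result is "a sample size of 23 patients per arm was calculated using the R package", computed with a t "test for two independent samples", and then "Assuming a drop-out rate of 20%, the total number of patients needed per arm is 29", which makes 58 in total.

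The Statistical analysis section names a different test: "For analysis of the primary outcome, a Mann-Whitney" U test. The Primary endpoint section defines the scale as a 100-mm line running from 0 to 10, so a difference of 1 is one tenth of the scale, in the same range as the quoted means.

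**The concern.** The section quotes an SD of 1.7 in both arms and then plans with an SD of 1, without explaining the change. The second source does not supply the missing SD. As the protocol reports it, that source sets a unit standardized effect as the criterion of relevance; the SD of one is part of that definition and is not presented as an observed spread of pain scores.

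Two different targets are thereby treated as one. A standardized effect of 1 and a difference of 1 VAS point coincide only at SD 1. If the SD is near 1.7, the trial is sized for 1.7 points, and the 90% does not apply to 1 point. At stake is how the primary result is read. Someone who takes the section at its word would believe that the trial had 90% power for a 1-point benefit, and would weigh a non-significant result accordingly.

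**Working it through.** **Inputs.** Two-sided α 0.05, power 0.90, t test, 23 evaluable and 29 randomized per arm, and design effect 1/1 are from the Sample size section. So are the quoted difference, 5.7 − 4.2 = 1.5 points, and the quoted SD of 1.7 in each arm. The Mann-Whitney test is from the Statistical analysis section.

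**Formula.** With standardized effect d = difference / SD and n per arm, t-test power is the probability that a noncentral t variable with 2n − 2 degrees of freedom and noncentrality d·√(n/2) exceeds the two-sided 5% critical value in absolute size. Mann-Whitney power was simulated with normal data.

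**1. The plan's own figure.** d = 1/1 = 1. Solving for 90% gives n = 22.02, rounded up to 23. Noncentrality is 1 × √11.5 = 3.39 and power at n = 23 is 91%. Drop-out: 23 / 0.80 = 28.75, rounded up to 29 per arm, 58 in total. All three numbers reproduce.

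**2. What d = 1 means in points.** At SD 1.7 it is 1 × 1.7 = 1.7 points, against 1.5 observed in the quoted study. That study's own standardized effect is 1.5 / 1.7 = 0.88.

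**3. Power at SD 1.7.** For a literal 1 point, d = 1 / 1.7 = 0.59.

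| Difference | d | Evaluable per arm | Noncentrality | t test | Mann-Whitney |
|---|---|---|---|---|---|
| 1.5 points | 0.88 | 23 | 2.99 | 83% | 81% |
| 1.5 points | 0.88 | 29 | 3.36 | 91% | 89% |
| 1 point | 0.59 | 23 | 1.99 | 50% | 47% |
| 1 point | 0.59 | 29 | 2.24 | 60% | 57% |

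The Mann-Whitney figures carry simulation error of up to about one percentage point.

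**4. Evaluable patients per arm for 90% at SD 1.7 (t test).** For 1.5 points, 27.99, so 28 (28 / 0.80 = 35 randomized per arm, 70 in total). For 1 point, 61.7, so 62 (62 / 0.80 = 77.5, so 78 per arm, 156 in total).

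**5. Difference detectable with 90% power at SD 1.7 (t test).** About 1.66 points with 23 per arm and 1.47 points with 29.

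**6. Sensitivity to the SD.** Power for 1 point with 23 per arm (t test):

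| SD | 1.0 | 1.3 | 1.5 | 1.7 | 2.0 |
|---|---|---|---|---|---|
| Power | 91% | 72% | 60% | 50% | 38% |

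**7. Choice of test.** At d = 1 with 23 per arm, Mann-Whitney has about 89% power, close to the stated 90%.

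**The case against.** The strongest reply is that t-test power depends only on the ratio, that the ratio was set to 1 on the authority of a cited source, and that for this ratio the numbers are right. This stands as far as it goes: it would be wrong to call the calculation an arithmetic error, or to say that the effect size has no cited basis. It does not rescue the translation into 1 VAS point, which needs an SD that the section never reports as observed.

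Three further replies limit the size of the point:

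- **The 50% is a hybrid.** It combines the 1 point in the design assumption with the SD of another study, and the protocol nowhere posits that pair. The like-for-like comparison is 0.88 against 1, which gives 83%. This stands, so the 1-point figure belongs in a sensitivity statement.
- **The SD of 1.7 may not apply.** It comes from right-sided hemicolectomy in a matched cohort, and the Sample size section does not say that it was measured during mobilization or at 24 hours. This also stands. However, at SD 1.3 or 1.5 power for 1 point is still only 72% or 60%.
- **23 per arm may be pessimistic.** Patients are randomized during the operation and the endpoint is taken in hospital 24 hours after surgery, so a 20% loss seems unlikely. With all 29 evaluable, power for 1.5 points is 91% by t test. This is a fair argument for leaving the trial size alone, although 20% is the plan's own assumption.

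A reader might infer that the trial is badly underpowered, with only even odds of success, or that 58 patients must be increased. The document does not support either. Even odds hold only for a 1-point difference at SD 1.7 with 23 evaluable per arm, and for the effect actually quoted 58 patients come close to the target. Nor does the protocol say that a non-significant result will be taken to exclude a 1-point difference; that is a risk of misreading, not a stated plan.

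**Conclusion.** The point holds as a mis-stated planning assumption. The counts 23, 29 and 58 follow from a standardized effect of 1, but the section presents that effect as 1 VAS point, against the only observed SD that it quotes and without explanation.

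If the SD is 1.7, the shortfall for the quoted 1.5 points is moderate with 23 evaluable per arm and essentially absent with 29. For a literal 1-point difference it is large with either number, but that figure depends on an SD borrowed from another operation. These results assume normally distributed scores with equal SDs and equal arms.

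The mismatch between the t test used for sizing and the planned Mann-Whitney test costs one to three percentage points in these settings and does not deserve a separate point. This is a correction to make in the text, not a defect that invalidates the design.

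**What to change.** Keep 58 patients and revise the Sample size section as follows:

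1. Delete the equation of the standardized effect with a 1-point difference and an SD of 1, or justify an SD of 1 for pain during mobilization at 24 hours.
2. Restate the power at SD 1.7 under the planned test. Possible wording: *Assuming an SD of 1.7, a Mann-Whitney test at the two-sided 5% level has about 81% power to detect 1.5 VAS points with 23 evaluable patients per arm and about 89% with 29; for 1 point the power is about 47% and 57%.*
3. Add the difference detectable with 90% power (t test, SD 1.7): about 1.66 points with 23 per arm and 1.47 points with 29.
4. State that the primary result will be interpreted through a confidence interval for the difference in VAS points, so that a non-significant result is not read as excluding differences that the interval still contains.

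The cost is text only, with no change to recruitment or to the primary test. The downside is that the stated power becomes less favourable. If 90% power for 1.5 points is still wanted after 20% drop-out, the total would be 70 (t test), which is a separate decision for the investigators.
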